### Housing stability and hospitalizations

We will assess housing stability and hospitalizations among HEVs during and after receiving aftercare services, comparing: (a) REP versus enhanced REP sites and (b) the 32 implementation sites with a control group of 32 sites that did not implement CTI, matched on geographic setting and number of case managers. We will use administrative data (from VA’s Corporate Data Warehouse [CDW] and homeless registry) to assess these outcomes (Table 3).

**Table 3 Tab3:** Summary of quality metrics assessed using VA administrative data

Domain	Quality metric
Housing stability	• Number of days between aftercare entry and first VA indicator of housing instability^a^ • Annual number of encounters with VA homeless services • Annual number of discrete episodes^b^ of engagement with VA homeless services
Hospitalizations	• Number of days between aftercare entry and first hospitalization (VA or non-VA) • Annual number of hospitalizations (total and separated into medical/surgical versus mental health) • Annual number of hospital bed days
Outpatient service use	• Primary care provider assignment (yes/no) • Presence or absence of at least one primary care visits/year • Use of VA vocational services (among HEVs seeking employment) • Total number of mental health visits (among HEVs with mental health disorders) • Total number of substance use disorder treatment visits (among HEVs with substance use disorders)

^a^Use of VA homeless services

^b^New episodes desfined by 30 days passing between encounters

For all HEVs who enter implementation and control sites between 6 and 18 months post-implementation (the time during which we have captured fidelity), we will determine the number of days between aftercare entry and the first VA indicator of housing instability (i.e., homeless service use). Within each cohort, for sites that receive REP or enhanced REP to support CTI implementation, we will use survival analysis (Cox proportional hazards models) to compare time to the first presence of a housing instability indicator among those who received aftercare in the same period in matched control sites. Models will use clustered robust standard errors to account for potential within-site correlation. We estimate that there will be 4,080 HEVs split evenly between implementation and control sites (~64 HEVs/site). Using a two-sided alpha level of 0.05, we estimate having 80% power to detect a 25% relative difference in time to housing instability indicators. This estimate is based on a log-rank test, assuming an intraclass correlation within each site of ~0.05.

Within implementation sites, we will assess for independent associations between housing instability among HEVs and sites’ assigned implementation strategy (REP versus enhanced REP) and CTI fidelity. We will also compare HEVs between implementation and control sites; per HEV, we will compare the annual number of encounters with VA homeless services (a proxy for service intensity needed) and the annual number of episodes of homeless service engagement (with new episodes defined by ≥30 days between encounters). Comparisons will be made using negative binomial regression models with clustered robust standard errors for site-level clustering.

Similarly, we will determine, for each HEV, the days between entry into aftercare and hospitalization (at the VA or paid for by VA at an outside hospital) and describe the time to hospitalization using Kaplan-Meier curves. We will include all hospitalization types (mental health, medical/surgical), analyzing the time to any hospitalization and by type. We will also assess for independent associations between these outcomes and implementation strategy and CTI fidelity using Cox proportional hazards models. Additional secondary outcomes will be the annual number of hospitalizations (total and by type) and the number of bed days per HEV. We will also assess time trends in housing stability and hospitalizations within implementation sites, comparing pre- and post-implementation.

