### Participating sites

Our partners at the GPD National Program Office identified 7 priority VA regions (Veterans Integrated Services Networks [VISNs]) for CTI implementation in aftercare. We will engage with VA homeless program leaders in these VISNs, and their associated VA facilities, to identify 32 aftercare sites across three cohorts, with 10–11 sites per cohort. Sites for each cohort will be identified in the 3 months prior to cohorts’ implementation initiation, based on sites self-identifying as being ready for implementation. Of note, our sample size (32 sites) was pre-determined by our funder.

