### Study design

We plan a type 3 hybrid implementation-effectiveness trial [13], registered as NCT05312229 on April 4, 2022, and determined to be non-research by VA’s Central Institutional Review Board. Given distinct leadership, staffing, and policies by site, and the high likelihood of contamination among case managers within sites, cluster randomization will occur at the site level. Within each cohort, the implementation team will use permuted block randomization—with geographic setting (urban, suburban, and rural) and number of case managers (a proxy for site size and resources) as stratification factors—to balance these factors among sites receiving REP versus enhanced REP. Figure 5 depicts a Consolidated Standards of Reporting Trials (CONSORT) flow diagram of our comparison groups. We will also use the stratification factors to match each of the 32 implementation sites to a control aftercare site not implementing CTI. Data from control sites will be used to assess selected quality metrics and costs of CTI as implemented. The CONSORT 2010 checklist of information for randomized controlled trials is available as supplemental material.

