### Costs and return-on-investment (ROI)

We will estimate the costs and ROI of CTI implementation in aftercare from the perspective of VA; costs associated with non-VA homeless and healthcare services are outside the scope of these analyses. We will compare costs at sites that receive REP versus enhanced REP and calculate the ROI of CTI implementation, as compared to control sites. In addition to implementation costs, CTI may lead to increased VA costs associated with enhanced outpatient service use but decreased costs associated with inpatient care. There may also be decreased costs from VA homeless services as veterans retain permanent housing.

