#### ROI of CTI and implementation strategies

The financial ROI of CTI and these implementation strategies depends on savings reaped through improved housing stability and decreased hospitalizations. To calculate the degree of cost offsets, we will link HEVs’ use of VA housing and health services to the costs of these activities which are available in an activity-based cost allocation system (the Managerial Cost Accounting System) [28]. Among HEVs who enroll at implementation sites between 6 and 18 months after the initiation of CTI implementation, we will calculate mean housing and health services costs per HEV in the 6, 12, and 18 months after enrollment. We will use a multivariable generalized linear model and two-part regression models where appropriate to compute ROI at 6-, 12-, and 18-month time horizons for HEVs in sites that received REP versus enhanced REP, and compared to the 32 control sites. We will compare model fit using a generalized linear model and ordinary least squares [29].

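### The non-randomized CTI-versus-control comparison and the ROI of CTI use post-implementation data only, so systematic differences between self-selected ready sites and controls are not separated from a CTI effect

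*Protocol article*

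**What the plan says.** All of this is in the Methods of the protocol article.

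- **Choice of implementation sites** (Participating sites): the program office "identified 7 priority VA regions", and sites within them enter "based on sites self-identifying as being ready for implementation".
- **Choice of controls** (Study design): "We will also use the stratification factors to match each of the 32 implementation sites to a control aftercare site not implementing CTI". Housing stability and hospitalizations repeats the two factors: "a control group of 32 sites that did not implement CTI, matched on geographic setting and number of case managers". Neither section states a readiness, region or baseline-outcome criterion for controls.
- **Outcome window** (same section): the time-to-instability analysis is defined "For all HEVs who enter implementation and control sites between 6 and 18 months post-implementation". The comparator is veterans in matched control sites over the same period, analysed by Cox models with site-clustered robust standard errors. Annual encounter and episode counts are compared by negative binomial models.
- **Pre-implementation outcomes** (same section): "We will also assess time trends in housing stability and hospitalizations within implementation sites, comparing pre- and post-implementation".
- **ROI**: the plan is to "calculate the ROI of CTI implementation, as compared to control sites". For veterans enrolling in the 6-to-18-month window, "we will calculate mean housing and health services costs per HEV in the 6, 12, and 18 months after enrollment" (ROI of CTI and implementation strategies).

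**The concern.** Two analyses bear on whether CTI works, and each leaves open what the other closes. The same-period control contrast removes calendar-time changes shared by both groups, but not systematic differences that existed before CTI. The pre/post contrast removes stable site differences, but not calendar time, because no control trend accompanies it. The plan describes no analysis that joins them.

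Such a difference is plausible. Readiness decides which sites implement, and it is not a matching factor. The two matching factors are the randomization strata reused.

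A decision hangs on the result. The contrast supplies the ROI of CTI and the business case for its spread, and the stated goal is all 128 aftercare sites. The limitations in the Discussion cover generalizability, the funder-set sample size and the cost of the strategies. They do not mention selection of implementation sites relative to controls.

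**Working it through.** **Inputs from the article (Housing stability and hospitalizations).** 4,080 veterans split evenly over 64 sites, two-sided alpha 0.05, 80% power for a 25% relative difference, log-rank test, ICC about 0.05.

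**Assumptions.** The article gives neither a hazard ratio nor an event proportion. I read the 25% difference as HR 0.75 and show a range of event proportions. The pre-existing site-group hazard ratios below are also assumed; nothing in the article gives one.

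**1. The plan's own figure**
- Veterans per site: 4,080/64 = 63.75, which agrees with about 64.
- Design effect: 1 + (63.75 − 1) × 0.05 = 4.1375. Effective N: 4,080/4.1375 = 986.
- Effective events for 80% power at HR 0.75 (Schoenfeld): 4 × (1.960 + 0.842)² / (ln 0.75)² = 379.4, or 380. This is about 38.5% of 986.
- Read as HR 0.80 or 1.25, the requirement is 631 events, about 64%.

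So 80% is attainable but can be neither confirmed nor refuted. At 20% events the power for HR 0.75 would be 52%.

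**2. Selection alone, no CTI effect**

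SE(log HR) = 2/√379.4 = 0.1027. With b the pre-existing hazard ratio and t = |ln b|/SE, the rejection probability is Φ(t − 1.96) + Φ(−t − 1.96).

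| Pre-existing HR (assumed) | 20% events | 38.5% events | 64% events |
|---|---|---|---|
| 1.00 | 5% | 5% | 5% |
| 0.95 | 6.5% | 8% | 10% |
| 0.90 | 11.5% | 18% | 26% |
| 0.85 | 21% | 35% | 53% |

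A pre-existing HR of 0.90 is ln 0.90/ln 0.75 = 37% of the target log hazard ratio. The Cox comparison is described as within each cohort. With one third of the events, SE = 0.1027 × √3 = 0.178, and the 0.90 row becomes about 9%.

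**3. The opposite direction**

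Suppose implementation sites start worse by the same amount (HR 1/0.90) and CTI truly achieves 0.75. The expected log HR is −0.2877 + 0.1054 = −0.1823, so t = 0.1823/0.1027 = 1.775. Power falls from 80% to Φ(1.775 − 1.96) = 43%.

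**4. Precision after adding a control pre-period**

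Assume a pre-period of equal size, a linear approximation for site means, and site-level autocorrelation c between periods.
- Post-only variance of a site mean, relative to total variance: v = 0.05 + 0.95/63.75 = 0.0649.
- Difference-in-differences: 2 × [0.05(1 − c) + 0.95/63.75]/v.
- Baseline adjustment: 1 − (0.05c/v)².

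| c (assumed) | Difference-in-differences | Baseline-adjusted |
|---|---|---|
| 1.0 | 0.46 | 0.41 |
| 0.8 | 0.77 | 0.62 |
| 0.5 | 1.23 | 0.85 |

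Values below 1 mean better precision than the post-only contrast. At 1.23, a comparison with 80% power falls to Φ(2.802/√1.23 − 1.96) = about 71%.

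**The case against.** A reader might infer more than the article supports.

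- **That the trial's main result is biased.** It is not. REP and enhanced REP are randomized between sites, fidelity is the primary outcome, and CTI's effectiveness is observed alongside. Comparisons between the two strategies do not use the controls.
- **That every prior difference, and any secular change, is credited to CTI.** Chance differences between sites are covered by the clustered standard errors and the ICC; only systematic selection biases the contrast. Shared secular change is already handled by same-period controls. The pre/post analysis is described as a time trend, and the article does not say the change will be attributed to CTI.
- **That the bias favours CTI.** Ready sites may start better. But the regions were chosen as priorities, and the Background mentions sites with quality gaps, so a real benefit could be masked. The regions from which controls come are not stated, so a regional imbalance is not established.
- **That covariate adjustment is absent.** The ROI model is called multivariable, and covariate lists commonly sit in a fuller plan. That omission is no finding. Adjustment for veterans' characteristics would not by itself remove a difference in site readiness.
- **That difference-in-differences cures the problem.** It removes stable differences only. Volunteering when ready is partly time-varying, and parallel trends must be assumed.

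These points narrow the concern without answering it: neither planned analysis separates systematic prior site differences and calendar time together from CTI.

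**Conclusion.** The concern holds for the secondary, non-randomized CTI-versus-control comparison, the ROI of CTI and the business case built on it. The text fixes readiness-based selection, two matching factors, a post-only window and a pre-period for implementation sites alone. It is a weakness of design that should be repaired; the separate analyses are not themselves miscalculated.

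Neither the size nor the direction of the bias can be derived from the article. The figure of about 18% is one illustration, resting on an assumed pre-existing HR of 0.90, HR 0.75 as the target and the stated 80% power. It should be quoted with its range of 11.5% to 26% over 20% to 64% events.

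**What to change.** 1. Extract the same administrative data for the 32 control sites over the same pre-implementation calendar window as their matched implementation sites.
2. Choose entry dates, or censor follow-up, so that pre-period outcomes and costs end before implementation starts. This matters most for ROI: with an 18-month cost horizon, anyone enrolled in the 18 months before implementation has costs that run into the CTI period.
3. Estimate the CTI effect as the group-by-period term, or with adjustment for the site's baseline outcome, for time-to-event, count and cost outcomes.
4. Show pre-period trends by group, and keep the post-only contrast as a supporting analysis.
5. Label the CTI effect and ROI as observational, since time-varying readiness remains, and add this to the limitations.

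Cost: a longer pull from administrative sources already in use, plus programming; no new sites or primary data collection. The article refers to a national aftercare roster and already uses the program's roster to find pre-implementation users, so the data should exist, but availability for control sites needs checking. The interval may widen under difference-in-differences if sites' pre and post rates correlate weakly (relative variance about 1.23 at an assumed autocorrelation of 0.5). Baseline adjustment avoids that loss (about 0.85), but does not fully cancel stable differences as difference-in-differences does.

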## Methods

### Overview

We hypothesized that enhanced REP will have higher implementation costs than REP, but enable increased tailoring to local contexts that results in stronger CTI implementation and effectiveness, supporting a business case for enhanced REP. To test this hypothesis, we will use a type 3 hybrid implementation-effectiveness trial [13]; this design tests the impacts of implementation strategies while gathering data regarding an EBP’s impacts on clinical outcomes. Specifically, we will compare the impacts of REP versus enhanced REP on CTI implementation and sustainment, while observing CTI’s effectiveness on housing and health outcomes. In a cluster randomized design, we will assign 32 aftercare sites to REP (*n*=16) versus enhanced REP (*n*=16), clustering sites in three implementation cohorts staggered in 9-month intervals.

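### Veteran-level models rely on cluster-robust standard errors with 32 sites (REP versus enhanced REP) or 20–22 sites (per-cohort Cox models), where the default form is mildly anti-conservative; a small-sample method should be fixed and site clustering made explicit for hospitalisation and cost

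*Protocol article*

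**What the plan says.** Under Housing stability and hospitalizations, the article names its variance method twice. For the time-to-housing-instability Cox models: "Models will use clustered robust standard errors to account for potential within-site correlation". For the annual counts: "Comparisons will be made using negative binomial regression models with clustered robust standard errors for site-level clustering". No finite-sample correction or reference distribution is named.

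The number of sites behind each model follows from the text:
- **REP versus enhanced REP:** 32 randomised sites, 16 per arm (Overview).
- **Implementation versus control, overall:** 64 sites, since the article compares "the 32 implementation sites with a control group of 32 sites that did not implement CTI".
- **Implementation versus control, per cohort:** the housing Cox model is introduced as "Within each cohort, for sites that receive REP or enhanced REP to support CTI implementation, we will use survival analysis (Cox proportional hazards models"), set against matched controls. Participating sites plans to "identify 32 aftercare sites across three cohorts, with 10–11 sites per cohort", so with one control per site each such model has 20–22 sites.

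For time to hospitalisation the article says: "We will also assess for independent associations between these outcomes and implementation strategy and CTI fidelity using Cox proportional hazards models". For costs: "We will use a multivariable generalized linear model and two-part regression models where appropriate to compute ROI". Neither place repeats the statement on clustering.

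**The concern.** The usual cluster sandwich estimates the between-site variance from the sites themselves. With few sites it is biased downward, and the normal critical value of 1.96 then ignores the uncertainty in the estimate. Both effects push p-values down. Unequal site sizes make this worse, and they are likely here: Study design uses the number of case managers as a stratification factor because it stands for site size and resources.

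The comparisons affected are the randomised veteran-level contrast and the per-cohort comparisons of CTI with controls. Business case analysis sets cost offsets and other benefits against the cost of external facilitation to decide whether enhanced REP should be preferred. Overstated precision in these secondary outcomes would therefore feed into that recommendation. The hospitalisation and cost outcomes come from the same veterans in the same sites, so they need the same treatment of clustering.

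**Working it through.** **Inputs.** From Housing stability and hospitalizations: 4,080 veterans in 64 sites (63.75 per site), intraclass correlation about 0.05, two-sided alpha 0.05, 80% power for a 25% relative difference. The article gives neither an event proportion nor the spread of site sizes, so both are assumed below.

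**1. The plan's own power figure.** Design effect = 1 + (63.75 − 1) × 0.05 = 4.14. Reading the 25% difference as a hazard ratio of 0.75, the Schoenfeld formula gives 4 × (1.96 + 0.842)² / (ln 0.75)² ≈ 380 events. Inflated: 380 × 4.1375 = 1,572, or 38.5% of 4,080. Without a stated event proportion the 80% can be neither confirmed nor refuted. It does show that 40% events is a reasonable working assumption.

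**2. Hand calculation.** Take G equal-sized sites, split evenly on one site-level factor. The uncorrected sandwich is then too small by a factor of about (G − 2)/G, and the statistic behaves like a t on G − 2 degrees of freedom. A test at 1.96 has error

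P( |t(G−2)| > 1.96 × √((G−2)/G) ).

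- G = 64: cut-off 1.929, error 5.8%
- G = 32: cut-off 1.898, error 6.7%
- G = 22: cut-off 1.869, error 7.6%
- G = 20: cut-off 1.859, error 7.9%

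**3. Simulation of null Cox models** (64 veterans per site, 40% events, intraclass correlation about 0.05). Type I error at nominal 5%, uncorrected sandwich with normal reference:

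| Setting | 64 sites | 32 sites | 20–22 sites |
|---|---|---|---|
| Gamma site effect, equal sizes (4,000–8,000 runs) | 5.4% | 7.3% | 7.3–7.7% |
| Log-normal site effect, size variation 0 to 0.6 (2,000 runs) | – | 5.7–8.1% | 7.4–9.7% |
| Further null simulation | about 5.7% | 6.8–7.8% | 6.6–10.3% |

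Monte Carlo error in the first row is about 0.3–0.4 percentage points. In the second it is about 0.6, from √(0.07 × 0.93 / 2,000).

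**4. With a simple correction.** Multiplying the variance by G/(G − 2) and using t on G − 2 degrees of freedom gives, with equal sizes, 4.9% at 64 sites, 5.4% at 32 and 4.6–4.9% at 20–22. The further simulation gives 4.9–5.8% at 32 sites and 4.2–6.9% at 21. A lighter rescaling, G/(G − 1) with t on G − 2, leaves 4.3–6.5% at 32 sites and 5.3–7.3% at 22 under the log-normal setting. Some excess can therefore remain when sites are unequal.

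**5. If clustering were left out altogether.** The standard error would be understated √4.1375 = 2.03-fold, and the error would be 2 × [1 − Φ(1.96 / 2.03)] = 33.5%; the simulations give 32–39%. This uses the housing intraclass correlation. None is given for hospitalisation or cost. At 0.01 the design effect is 1.63 and the error 12%; at 0.02 they are 2.26 and 19%.

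**The case against.** The strongest reply is that the article is condensed. Corrections for few clusters, and the variance method for each secondary model, commonly sit in an analysis plan, which is not shown. The text commits to neither an uncorrected sandwich nor a normal reference. This stands as far as it goes: silence is not a stated error, and the inflation is conditional on the default form being used. But the article did choose to name the estimator, and that estimator's default form falls short at the article's own site counts. Settling the point is cheap.

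A reader might infer more than the text supports:
- **That every model has only 32 sites.** Pooled implementation versus control has 64, where the inflation is negligible.
- **That hospitalisation and cost are analysed without clustering.** The article does not say so. The hospitalisation paragraph sits under the same heading and opens by likening its method to the one just described. The cost section is merely silent, and it states no significance test for ROI.
- **That strategies are compared within a cohort at about 5 sites against 5.** The article places REP versus enhanced REP within the implementation sites, with no per-cohort restriction.

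It is also fair to say that stratifying and matching on number of case managers helps to balance site size between groups, and that the upper ends of the ranges rest on an assumed size variation of 0.6. The specific bias-corrected sandwiches recommended below were not simulated here. The case for them is that simpler rescaling can leave some excess when sites are unequal.

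**Conclusion.** The point holds as a conditional, moderate concern about secondary veteran-level analyses. If the clustered robust standard errors are used in default form, type I error is about 7–8% for REP versus enhanced REP and about 7–10% for the per-cohort implementation–control Cox models, instead of 5%. This rests on an intraclass correlation of about 0.05 (the article's), 40% events and site-size variation of 0 to 0.6 (both assumed). The pooled 64-site comparison stays at about 5.5–6%, and the primary outcome, a t-test on site-level fidelity scores, is not touched.

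For hospitalisation and cost, the documents support only a request to state the clustering explicitly. An error of about one third, and intervals about half the proper width, would follow only if clustering were truly omitted and the housing intraclass correlation applied. Nor can it be said outright that the trial's p-values will be too small, because that depends on a choice the article leaves open.

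**What to change.** - For the REP versus enhanced REP and per-cohort veteran-level models, specify a bias-corrected cluster sandwich (Kauermann–Carroll/CR2 or jackknife) with a t reference on sites minus site-level parameters.
- Pool cohorts where possible, with cohort as a stratum. For one strategy contrast this leaves 32 − 3 − 1 = 28 degrees of freedom, or 27 if CTI fidelity enters the same model. For implementation versus control, pooling restores 64 sites and removes most of the problem.
- Check the randomised contrast with a site-level permutation test that follows the actual randomisation: within cohort, respecting the strata.
- State that the hospitalisation Cox models and the cost/ROI models also account for site, for example by resampling whole sites in a bootstrap for ROI intervals.

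The cost is wording and standard software options. Intervals widen slightly: with equal sites, the factor is t(G−2)/1.96 × √(G/(G−2)), which is 1.08 at 32 sites and 1.12–1.13 at 20–22.

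### The 80% power for time to housing instability fits a pooled 64-site comparison with controls, not the within-cohort Cox analysis as written, and does not extend to REP versus enhanced REP

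*Protocol article*

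**What the plan says.** All of this is in the Protocol article. Under Housing stability and hospitalizations, two comparisons are announced: (a) REP versus enhanced REP sites, and (b) the 32 implementation sites versus 32 matched control sites.

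The time-to-event analysis is introduced with "Within each cohort, for sites that receive REP or enhanced REP to support CTI implementation, we will use survival analysis", using Cox models with matched control sites as the comparator. On clustering it says "Models will use clustered robust standard errors to account for potential within-site correlation". The power statement follows: "We estimate that there will be 4,080 HEVs split evenly between implementation and control sites (~64 HEVs/site"), then "Using a two-sided alpha level of 0.05, we estimate having 80% power to detect a 25% relative difference in time to housing instability indicators", based on a log-rank test and "assuming an intraclass correlation within each site of ~0.05".

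The next paragraph examines REP versus enhanced REP within the implementation sites, with no power figure.

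Participating sites gives the cohort structure: the team will work "to identify 32 aftercare sites across three cohorts, with 10–11 sites per cohort". The same section and the Discussion say that the funder fixed the 32 sites.

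**The concern.** The power sentence and the analysis sentence describe different data sets. The first uses every site in the project. The second, as worded, uses one cohort at a time and would give three separate results with no stated way to combine them. A null result in one cohort could then be set against an 80% figure that does not belong to it.

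The randomized comparison is listed first for these outcomes and follows directly after the power statement. The abstract hypothesizes that enhanced REP improves quality metrics and so supports a business case. A reader could carry the 80% across to that comparison, which has half the sites.

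With 20 to 32 clusters, uncorrected cluster-robust standard errors also tend to be too small, so significant results would come somewhat too easily.

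**Working it through.** **Inputs from the article.** Two-sided alpha 0.05; power 80%; 25% relative difference; 4,080 HEVs split evenly; about 64 per site; ICC about 0.05; three cohorts of 10–11 implementation sites; 16 versus 16 sites randomized. The article does not give the share of HEVs with an event, or whether 25% means a hazard ratio (HR) of 0.75 or a time 25% longer (HR 1/1.25 = 0.80). Both are treated as assumptions.

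**1. Which data set the 80% uses.** 4,080 / 64 sites = 63.75 per site, matching the stated figure of about 64. So the total needs all 64 sites. One cohort with its controls has 20–22 sites and about 4,080 / 3 = 1,360 HEVs. The randomized comparison has 32 sites and about 2,040.

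**2. Trying to reproduce the 80%.**
- Design effect: 1 + (63.75 − 1) × 0.05 = 4.1375. Effective sample: 4,080 / 4.1375 = 986.
- Events needed (Schoenfeld): 4 × (1.960 + 0.842)² / ln(HR)². HR 0.75 gives 380; HR 0.80 gives 631.
- Event share needed with the design effect applied to persons: 380 / 986 = 38.5% at HR 0.75; 631 / 986 = 64.0% at HR 0.80.
- With the design effect applied to events per site instead, the shares are 12.6% and 29.0%.

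The 80% is attainable under plausible inputs, but it can be neither confirmed nor refuted.

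**3. Scaling the 80% to fewer sites.** With effect, ICC, site size and event share unchanged, the expected test statistic is (1.960 + 0.842) / √k when 1/k of the sites are used. Power is Φ(2.802/√k − 1.960). Once the 80% is taken as exact, this does not depend on the event share or HR.
- One cohort, k = 3: Φ(1.618 − 1.960) = 36.6% (34.7% with 20 sites, 37.5% with 22).
- REP versus enhanced REP, k = 2: Φ(1.981 − 1.960) = 50.8%.
- Pooled and stratified by cohort, k = 1: 80%.
- With a t reference on sites minus 2 degrees of freedom: about 34%, 48% and 79% respectively.

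**4. Effect detectable with 80% power.** HR^√k gives, from HR 0.75, 0.67 for 16 versus 16 sites and 0.61 for one cohort. From HR 0.80 it gives 0.73 and 0.68.

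**5. If the 80% is not exact.** At HR 0.75 with the design effect on persons, event shares from 20% to 100% give:

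| Comparison | 20% | 50% | 100% |
|---|---|---|---|
| Pooled, 64 sites | 52% | 89% | 99.5% |
| 16 versus 16 sites | 30% | 62% | 89% |
| One cohort | 21% | 45% | 74% |

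**6. Standard errors.** Null simulations under assumed inputs (such as exponential times, a site frailty and 38.5% with an event; 4,000 trials per setting) gave a type I error with plain site-clustered robust errors of roughly 6–8% at 32 sites and 7–11% at 20–22 sites. A G/(G − 2) correction, with G the number of sites, and a t reference brought it to about 4–7%.

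**The case against.** The strongest defence is that one pooled analysis was intended. Cohorts start 9 months apart, so the cohort phrase may only mean that each cohort is matched to controls over the same calendar period. Comparison (b) is framed over 32 and 32 sites, and the power calculation counts all 4,080 HEVs. On that reading about 80% stands. This is plausible, but the article does not say it, and the sentence as written describes separate cohort analyses.

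A reader might infer that the trial's real power is 37% and 51%, or that the article claims 80% for its randomized comparison. The documents support neither. Both percentages assume the 80% is exact, and step 5 shows how far they move if it is not. The 37% also needs the separate-cohort reading, and the 51% borrows a 25% effect that the article never sets between two active strategies. The power sentence is tied to implementation versus control, and the site number is openly attributed to the funder. So the 51% marks the limit of what the figure covers; it does not correct a wrong figure.

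The choice of small-sample correction is often left to an analysis plan, and the wording does not rule one out. The 20–22 site error rates matter only if cohorts are analysed separately. The 32-site comparisons have few clusters on any reading.

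**Conclusion.** The point holds as a mismatch between the described analysis and the stated power, not as an arithmetic error. Taken literally, the within-cohort Cox comparison has less than half the stated power for the same effect and leaves no overall estimate. If a pooled cohort-stratified model is meant, the mismatch disappears once the text says so. For REP versus enhanced REP the article offers no power figure, and the 80% cannot stand in for one. These conclusions assume equal site sizes and the same ICC, effect and event share in each subset.

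Severity is moderate. The primary outcome is CTI fidelity, compared between sites by t-test, and nothing here touches it. The powered comparison is a secondary quality metric against non-randomized matched controls.

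**What to change.** Under Housing stability and hospitalizations:

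1. Replace the cohort wording with one Cox model over all 64 sites, comparing implementation with control sites, with the baseline hazard stratified by cohort.
2. State that the 80% applies only to this pooled contrast, and give the sponsor's own assumed event share and hazard ratio. The values derived above are checks on plausibility and should not be copied in as design parameters.
3. State separately, from the same inputs, the effect detectable with 16 versus 16 sites.
4. Specify small-sample-corrected site-clustered standard errors with a t reference on sites minus 2 degrees of freedom, mainly for the 32-site comparisons. The correction may not fully restore 5% when site sizes are very unequal.

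The cost is a change of wording, slightly wider intervals and a less favourable stated power for the randomized comparison. No sites or data are added.
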